### Tertiary outcomes

**
*1. Haemorrhage quantification by e-ASPECTS versus expert human readers.*
** We will use all RITeS NECT containing acute haemorrhage for this analysis. This includes scans acquired from haemorrhagic stroke trials (i.e. brain haemorrhages with or without intraventricular extension) in addition to scans classed as mimics in ischaemic stroke trials (e.g. subdural or subarachnoid haemorrhages).

Haemorrhage will be quantified by location and extent as follows.

*Haemorrhage location*

Haemorrhage location will be defined by side and gross anatomical regions of the brain affected including cerebral lobes (i.e. frontal, parietal, temporal, occipital), basal ganglia, brainstem, cerebellum, or extra-axial compartment (i.e. intra-ventricular, subarachnoid, subdural, extra-dural). We will convert e-ASPECTS haemorrhage detection overlay to these same 22 (11 per side) categories following visual review, blinded to human-reader results.

We will look at differences in the regions (and their number) identified by expert humans and e-ASPECTS and if the data are amenable, consider using methods that account for multiple concurrent haemorrhage sites per patient^52^.

*Haemorrhage extent*

Haemorrhage extent will require a comparison of haemorrhage volume calculated at the voxel level (e-ASPECTS) and haemorrhage dimensions used to estimate volume (i.e. the ABC/2 score^21^,^53^, human readers). We will use Bland-Altman testing (expected range of agreement to be within ± 10 mm^3^) and K-alpha statistics to test agreement between e-ASPECTS and human-rated results.

**
*2a. Impact of e-ASPECTS on diagnostic confidence and treatment decisions.*
** We will invite stroke and hospital admission physicians with a range of experience to complete an online questionnaire including RITeS NECT and relevant clinical scenarios, similar to previous work conducted by RITeS members^1^,^54^. We will compare responses for readers before and after ASPECTS is calculated (i.e. with and without e-ASPECTS overlay) to assess whether ASPECTS alters confidence in stroke diagnosis and determine its influence on management decisions.

RITeS cases with the following range of relevant radiological findings will be selected: with obvious, subtle and no ischaemic brain lesions (and a range of ASPECTS results); with and without hyperattenuating arteries; with subtle brain and extra-axial haemorrhage; with and without pre-stroke brain changes.

The questionnaire will contain 24 cases including some repetition of the same NECT with and without e-ASPECTS overlay. Specifically, we will include 10 cases shown with and also without e-ASPECTS overlay. To limit reader recognition of repeat cases, these images will be modified (e.g. left-right reversal, removal of any visible extracranial image components) and presented in a non-sequential order. We will also include two unique cases with and two unique cases without e-ASPECTS overlay; each of these 4 cases will be displayed only once. Thus 12 cases will be presented with and 12 without e-ASPECTS overlay. A unique clinical history will be provided for all 24 cases but we will limit clinical variability between repeat cases with and without e-ASPECTS overlay. Each case will include a panel of JPEG images representing the whole brain. Repeat images with and without e-ASPECTS overlay will include identical slices.

We will include up to three questions for each case:

1. Is the e-ASPECTS overlay helpful?• Yes• No2. Given the clinical history and the images presented, would you• Treat the patient immediately with IV alteplase (+/- refer for thrombectomy where available)• Refer the patient immediately for thrombectomy without IV alteplase• Not treat the patient with IV alteplase or thrombectomy but transfer to the acute stroke ward• I’m not sure, I’d first ask for a neuroradiology opinion• I’m not sure, I’d like to do more imaging such as angiography, perfusion imaging or MRI (not available here)3. How confident are you with this decision?• Very unsure• Unsure• Sure• Very sure

We will present these results as per Table 9, and visually in bar charts. We will compare results for the following subgroups in univariable analysis (chi-squared statistics): with versus without e-ASPECTS overlay, more versus less experienced readers, obvious versus subtle or no ischaemic lesion, with versus without haemorrhage, with versus without hyperattenuated arteries, with versus without leukoaraiosis, atrophy or old stroke lesions.

**
*2b. Use of e-ASPECTS/e-CTA and time required for scan interpretation.*
** We will select 100 NECT and 50 CTA from all RITeS cases that have been successfully processed by e-ASPECTS or e-CTA software, respectively and where expert human and software results match (to limit the likelihood that one test group is disadvantaged by known or unknown factors that make scan reading more difficult for either group). We will use stratified random sampling to ensure relevant scan appearances are equally represented as follows: From all available NECT with valid e-ASPECTS result we will create three stratai. No acute ischaemic lesion (i.e. ASPECTS = 10)ii. Small acute ischaemic lesion (ASPECTS 6-9)iii. Medium-large acute ischaemic lesion (ASPECTS 0-5)From all available CTA with valid e-CTA result we will create three stratai. No arterial obstructionii. Proximal ICA-MCA obstructioniii. Distal MCA obstruction

We will randomly sample similar numbers (i.e. one-third) from each of the three NECT and CTA strata (therefore ~33 cases for each NECT stratum and ~16 for each CTA stratum).

We will examine the performance of e-ASPECTS/e-CTA software versus: a. Radiology/stroke physician trainees, front-of-house clinicians (non-experts)b. Experienced stroke physicians or neuroradiologists (experts)

We aim to include a minimum of five expert and five non-expert readers. Each reader will be shown a unique random 10% selection (10 NECT and 5 CTA) of the cases on a PACS (picture archiving and communication system) workstation suitable for clinical review of DICOM imaging. If more than 10 readers are recruited to the study, we will allow repeat reading of cases. Readers will be asked to fully evaluate CT and CTA as required for routine stroke care using a standard proforma. Full evaluation will include assessment for all potential causes of stroke symptoms in any intracranial location (NECT – ischaemic brain lesion including ASPECT scoring, hyperattenuating artery sign, haemorrhage, mass lesion) and identification of arterial obstruction that might cause ischaemic stroke (CTA – including collateral scoring when relevant). All scan ratings will be performed blind to clinical characteristics, prior human reading and prior e-ASPECTS/e-CTA software results.

An observer will record the time taken (in seconds) for full NECT and CTA evaluation, as well as the time needed for ASPECT and CTA obstruction scoring alone. Software times will be measured from initiation of the software prior to scan loading to receipt of a valid output. Valid outputs include either an ASPECT score, identification of a hyperattenuated artery, or determination of arterial patency (i.e. to ensure a fair comparison, software errors will be excluded from this analysis).

We will compare the time needed for human (all, expert only, non-expert only) and software derived ASPECTS and CTA obstruction/collateral scoring separately in univariable analyses, i.e. Mann-Whitney U testing.

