## Figures and Tables

**Table 1. T1:** Clinical stroke trials with baseline CT scans available for inclusion in RITeS.

Stroke Trial	Number patients	Baseline CT Assessment	Stroke Type	Trial Type	Other Scans	Follow-up Data
ATTEST	104	ASPECTS	Isch	RCT – IV alteplase or tenecteplase	CT at 24–48 hrs	2 & 90 days
EuroHyp	98	As per IST-3, excluding CTA.	Isch	RCT – systemic cooling to 34-5°C for 24 hours or control	CT/MRI at day 5	0–7 & 90 days
IST-3	3035	Ischaemia extent & location, ASPECTS, swelling, atrophy, leukoaraiosis, old stroke lesions, arterial patency & collateral scores on CTA, scan quality 3.	Isch	RCT – IV alteplase or control	Baseline CTA (in ~270) CT/MRI at 24–48 hrs	7 days & 6- months
LINCHPIN	947 *	Location & size of intracerebral haemorrhage	Haem	Observational cohort study	MRI at 3 months	Post-mortem
PISTE	65	As per IST-3.	Isch	RCT – IV alteplase and thrombectomy or IV alteplase alone	Baseline CTA CT/MRI at 22–36 hrs	2 & 90 days
POSH	113	Ischaemia volume on CT, ASPECTS, arterial patency on CTA	Isch	Observational study	CT at 24–48 hrs	
PRACTISE	271	As per IST-3.	Isch	RCT – Multimodal CT imaging (CT + CTA + CTP) or CT alone	Baseline CTA (in 50%) CT/MRI at 24 hrs	1, 7 & 90 days
RESTART	537	Location & size of haemorrhage, atrophy, leukoaraiosis, old stroke lesions, scan quality	Haem	RCT – restart or avoid antiplatelets after haem stroke	MRI pre- randomization (in 550)	1–3 years
RIGHT-2	1149	As per IST-3.	Isch	RCT – ultra-early transdermal GTN or control	CT at 24–48 hrs	4 & 90 days, 1 year
SITS Open	293	ASPECTS, swelling, arterial patency on CTA	Isch	Controlled study -thrombectomy vs control	Baseline CTA (in ~5%) CT/MRI at 22–36 hrs	1, 7 & 90 days

* Ongoing at time of data collection.

**Table 2. T2:** Planned assessment of demographic and clinical data for non-stroke mimic cases within the RITeS dataset, and comparison with other datasets.

Clinical Feature		RITeS dataset	SSNAP dataset	STTC dataset	HERMES dataset	LATCH dataset
Total patient number			87,635	6,756	1,764	137
Female sex			48%	45%	47%	55%
Age, years			77 (66-85)	71 (13)	67 (57-76)	79 (67-83)
Aetiology	Ischaemia		87%	100%	100%	-
	Haemorrhage		12%	-	-	100%
NIH Stroke Scale			5 (2-11)	12 (7)	17 (13-21)	-
Glasgow Coma Scale			-	-	-	13 (9-15)
Time from stroke onset, hours			4 (2-11)	4 (1.2)	3 (2-4)	-

Note: Data are percentage, median (inter-quartile range), or mean (standard deviation) as appropriate.

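### The haemorrhage volume comparison pools parenchymal, ventricular and extra-axial blood and sets a voxel volume against ABC/2 without matching the compartments measured, so part of any disagreement may be definitional.

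*SAP article*

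**What the plan says.** In the SAP article, Tertiary outcomes, item 1, one analysis set serves both location and extent: "We will use all RITeS NECT containing acute haemorrhage for this analysis". The set is described as "brain haemorrhages with or without intraventricular extension" from the haemorrhagic stroke studies, plus bleeds classed as mimics in the ischaemic trials ("e.g. subdural or subarachnoid haemorrhages").

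Under Haemorrhage extent: "Haemorrhage extent will require a comparison of haemorrhage volume calculated at the voxel level (e-ASPECTS) and haemorrhage dimensions used to estimate volume". The human side is ABC/2. Agreement is judged by Bland-Altman, with an expected range of ± 10 mm³, and by K-alpha. The text has no restriction or stratum by compartment and no rule for applying ABC/2 to ventricular, diffuse or multiple bleeds. A conditional provision for several concurrent sites appears under Haemorrhage location only. That part also codes the software overlay into regions that include the ventricular, subarachnoid, subdural and extradural spaces.

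Table 1 lists the baseline reading in LINCHPIN (947 patients) as "Location & size of intracerebral haemorrhage". RESTART (537 patients) lists haemorrhage size without naming a compartment. The ischaemic trials list no haemorrhage size. Dissemination of results says that tertiary outcomes need further expert reading.

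**The concern.** A Bland-Altman analysis assumes that both methods aim at the same quantity. ABC/2 is half the product of three diameters and stands for a single, roughly ellipsoidal haematoma. Blood in the ventricles or spread through the subarachnoid space has no such three diameters. If the voxel volume counts that blood and the human figure does not, two correct readings differ by its full amount. The pooled bias then moves towards apparent over-measurement by the software, the limits widen, and K-alpha is lowered, none of which says how well the software measures a haematoma. Changing the agreement limit would not remove this.

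**Working it through.** **Inputs.** From the plan: the pooled set, the two measures and the ± 10 mm³ (0.01 mL) limit. The limit is chosen, not derived, so there is no figure to reproduce. The plan gives no bleed volumes and no share with ventricular blood, so all of these below are assumptions.

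**1. ABC/2 on a perfect ellipsoid.** True volume = (π/6)·ABC = 0.5236·ABC, while ABC/2 = 0.5·ABC. The ratio is 0.955, so voxel volume minus ABC/2 = 0.0451·V.

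**2. One scan.** Take a 30 mL lobar bleed with 15 mL of ventricular blood. ABC/2 = 0.955 × 30 = 28.6 mL. If the software counts the ventricular blood it reports 45 mL, a difference of 16.4 mL. If it does not, it reports 30 mL, a difference of 1.4 mL. The 15 mL between these depends wholly on what the software volume covers.

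**3. Pooled set, no software or reader error.** Let d = 0.0451·V + X. V is lognormal with median 15 mL and log-SD 0.9, so its mean is 15·exp(0.405) = 22.5 mL and its SD is 22.5·√(exp(0.81) − 1) = 25.1 mL. X is blood outside the ABC/2 figure: present with probability p, and then exponential with mean m.

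- Mean of d = 0.0451 × 22.5 + p·m = 1.0 + p·m.
- Variance of d = (0.0451 × 25.1)² + 2p·m² − p²·m² = 1.28 + 2p·m² − p²·m².
- For p = 0.2, m = 15: mean 4.0; variance 1.28 + 90 − 9 = 82.3; SD 9.07; limits 4.0 ± 17.8 = −13.8 to 21.8 mL.

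Simulation of 200,000 bleeds (bias; limits, in mL):

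| Share with such blood | m = 5 mL | m = 15 mL |
|---|---|---|
| 0% | 1.0; −1.2 to 3.2 | 1.0; −1.2 to 3.2 |
| 10% | 1.5; −3.3 to 6.3 | 2.5; −10.6 to 15.6 |
| 20% | 2.0; −4.3 to 8.3 | 4.0; −13.8 to 21.8 |
| 40% | 3.0; −5.2 to 11.2 | 7.0; −16.7 to 30.7 |

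With 10% random error in ABC/2, the limits without such blood are −5.7 to 7.7. At 20% and 15 mL they are −14.9 to 22.9.

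**4. Noisier assumptions.** Take log-SD 1, ABC/2 error 15%, and ventricular blood of median 8 mL (log-SD 0.8) in 0, 20 or 40% of bleeds. The mean difference is 0.8, 3.0 and 5.2 mL, with limits −10.9 to 12.6, −14.1 to 20.1 and −15.1 to 25.5. The half-widths are 11.75, 17.1 and 20.3. Ordinary ABC/2 error and scaling therefore supply (11.75/17.1)² = 47% of the variance at 20%, and (11.75/20.3)², about a third, at 40%. The mismatch supplies the rest.

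The falling lower limit comes from applying mean ± 1.96 SD to skewed data. Added blood cannot make any single difference smaller.

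**5. Subdural blood.** Model a crescent between two spherical caps on the same rim, each of volume πh²(3R − h)/3. Three such crescents give ABC/2 of 38.1 against a true 33.5 mL, 128.6 against 119.3 mL, and 48.0 against 44.2 mL: 14%, 8% and 9% too high. Crescents with outer radius 65–80 mm, diameter 90–100 mm and thickness 10 mm give 12–22% too high. A flat-based parabolic shape of 100 × 80 × 10 mm gives 40 against π × 50 × 40 × 10/2 = 31.4 mL, which is 27% too high. So a compact subdural can be sized, with an error that depends on shape and runs opposite to the ventricular effect.

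**6. The stated limit.** Setting 0.0451·V = 10 mm³ gives V = 222 mm³, or 0.22 mL. A perfect parenchymal ellipsoid of 10 mL already differs by 451 mm³.

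**The case against.** The strongest reply is that the text leaves open what each side measures. The compartments in the exported software volume are not stated, and coding the overlay by region belongs to the location analysis. The reading rule for ABC/2 may lie in the cited methods or a fuller protocol, and new expert reading is planned. Subarachnoid cases may have no ABC/2 value at all. Analysis principles says missing data are not imputed, so those cases would drop out instead of distorting the result. This stands as a limit on what can be claimed. It does not remove the point, because the plan itself sets the pooled set against ABC/2 and defines neither volume.

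A reader might infer more than the document supports:

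- That the software sums all blood voxels. This is plausible but inferred.
- That ABC/2 leaves every extra-axial bleed unmeasured. Step 5 shows otherwise for compact subdurals.
- That the difference is scored as software error. The extent analysis is worded as agreement; the reference-standard wording in Analysis principles concerns diagnostic accuracy.
- That the results would say nothing about the software. In step 4, ordinary measurement differences still make up a third to a half of the variance.
- That pooling decides whether the stated limit is met. By step 6 the limit fails without any pooling.

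Simply excluding the mixed bleeds would also remove harder cases from a study that aims at a real-world range.

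**Conclusion.** The point holds in a limited form. As written, the extent analysis mixes compartments and compares a voxel volume with a single-ellipsoid estimate. Where the software counts ventricular or diffuse subarachnoid blood, part of the bias, the limits and K-alpha reflects a difference of definition. Under the noise-free assumptions of step 3, the bias rises from 1.0 mL to between 1.5 and 7.0 mL, and the upper limit from 3.2 mL to between 6.3 and 30.7 mL. The direction follows from geometry if the software counts that blood. The size rests entirely on assumed volumes and shares, and no K-alpha value was computed. Subdural overestimation by ABC/2 could offset some of the bias. The outcome is tertiary and is reported after the main publication, so no primary or secondary result is affected. The correction is worth making because it is cheap and improves the analysis whatever limit is used.

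**What to change.** Amend Haemorrhage extent to:

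1. State which compartments the software volume covers and which bleed the reader measures for ABC/2.
2. Make the main volume-agreement analysis parenchymal haematomas without intraventricular or extra-axial blood on the expert reading, or compare the same compartment on both sides.
3. Report bleeds with ventricular or extra-axial blood as a separate stratum, neither pooled nor discarded, with the number lacking an ABC/2 value.
4. Keep all bleeds in the location analysis, as already planned.

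The cost is SAP wording and fewer scans in the main volume comparison. Matching compartments keeps more scans but needs a software volume by compartment, which the plan does not say is available. The ± 10 mm³ limit and its unit need review in their own right, since this change leaves that problem in place.

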## Statistical analysis

### Analysis principles and general considerations

Primary and where appropriate, secondary outcome testing will be conducted on an ‘intention-to-analyse’ basis irrespective of whether scan processing was successful or not◦ Processing will be considered successful when an ASPECTS (0-10) or CTA result (occlusion/no-occlusion or scalar collateral score) is provided, or when arterial hyperattenuation or haemorrhage is detected.◦ We will record all software failures whether these occur at the scan upload, scan processing, or results output stage.We will use mean (standard deviation, SD) or median (inter-quartile range, IQR) to represent the distribution of parametric and non-parametric data, respectively. We will use n (%) for categorical data.Where possible, we will use diagnostic accuracy statistics as the principal method in RITeS for comparing software and expert human results. With expert human results as the reference standard, we will calculate true/false positive/negative cases (TP, FP, TN, FN, respectively) and derive sensitivity (TP/TP+FN), specificity (TN/TN+FP), positive predictive (TP/TP+FP), negative predictive (TN/TN+FN), and accuracy (TP+TN/TP+TN+FP+FN) percentages as standard. We will calculate 95% confidence intervals for each using the Wilson score method^37^. ◦ For all diagnostic accuracy testing we will include random-effects meta-analysis modelling of individual patient data (i.e. a one-step meta-analysis) to provide overall estimates of sensitivity and specificity, to assess variation within and between the 10 RITeS studies, and to account for clustering of individual study results^38^,^39^.◦ For each of the 10 RITeS studies, we will use the PROBAST method for assessing risk of bias in diagnostic modelling^40^. For all comparisons of software and expert human results, we will review side of affected brain data to ensure ASPECTS and CTA results are correctly matched for each cerebral hemisphere, i.e. matched results require same score and side. We will separately test whether knowledge of affected side impacts the accuracy of e-ASPECTS results, see secondary outcomes below.Bland-Altman plots^41^ will be used to visually compare software and expert human results, comparing mean score differences to assess the magnitude, direction and distribution of error and will use ± 1.96 SD to determine the range of agreement^42^. For software and expert human results to be considered equivalent, we will set maximum clinically acceptable limits of agreement for individual scores, specified in the relevant sections below.Krippendorff’s Alpha^43^ (K-alpha) will be used to assess reader (human-human and human-software, as necessary) agreement. K-alpha is generally more robust than kappa in this context since it can handle categorical and ordinal data, works where there is missing data, adjusts for small sample sizes, and includes multiple observers simultaneously^43^,^44^. K-alpha results are interpreted similarly to kappa with scores ranging from -1 (perfect disagreement) to +1 (perfect agreement). We will therefore also use the Landis and Koch method for interpreting K-alpha results (as commonly used for kappa): 0.00–0.20=slight agreement, 0.21–0.40=fair agreement, 0.41–0.60=moderate agreement, 0.61–0.80=substantial agreement and 0.81–1.00=almost perfect agreement^45^.Other specific statistical tests are listed in the following sections.For multivariable testing, we will check for multicollinearity between included variables by identifying variance inflation factors (VIF) >5. Where multicollinearity is detected, we will run separate (but otherwise equivalent) multivariable regression models for each of the internally correlated variables.We will not impute but will report missing data (proportions of data missing for each variable and observations not included in analyses).We will use SPSS, IBM Corporation (Armonk, USA) and/or R (https://www.r-project.org/) statistical software for all analyses. We will preferentially report 95% confidence intervals, but where appropriate, we will report p-values.

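### The ±10 mm³ (0.01 mL) agreement limit for haemorrhage volume cannot realistically be met against human ABC/2, so even error-free software would be labelled not equivalent

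*SAP article*

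**What the plan says.** Under Tertiary outcomes, Haemorrhage extent, the SAP article sets "haemorrhage volume calculated at the voxel level (e-ASPECTS) and haemorrhage dimensions used to estimate volume" side by side. The human method is "the ABC/2 score". Agreement is judged by Bland-Altman analysis, with "expected range of agreement to be within ± 10 mm^3", and by Krippendorff's alpha. No reason is given for the figure of 10 or for the unit.

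The sample has no size restriction: "We will use all RITeS NECT containing acute haemorrhage for this analysis". It includes subdural and subarachnoid bleeds from the ischaemic stroke trials.

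Two statements in Analysis principles and general considerations give the limit its role. Bland-Altman analyses "will use ± 1.96 SD to determine the range of agreement". And: "For software and expert human results to be considered equivalent, we will set maximum clinically acceptable limits of agreement for individual scores", with the values to be found in the later sections. For volume, ±10 mm³ is the only value given.

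**The concern.** A limit of agreement is useful only if good software can pass it and poor software can fail it. Here the reference is a volume worked out from three linear measurements, and its error grows with the size of the bleed. A limit of one hundredth of a millilitre leaves almost no room for that error. If the reference alone uses up the whole limit, the equivalence label is fixed before any scan is processed and says nothing about e-ASPECTS.

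The SAP is meant to fix all methods before unblinding. If the limit is found to be unusable only after the volumes have been seen, any change to it will be a post hoc change of an equivalence margin, and possibly a very large one.

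**Working it through.** The SAP gives no derivation for the limit, so there is no figure to reproduce. The check is whether software with no error at all could meet it.

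**Inputs from the SAP.** Limit ±10 mm³; range of agreement = mean difference ± 1.96 SD; software volume counted from voxels; human volume = A × B × C / 2; all acute haemorrhages included; Table 3 provides for slices of ≤1 mm, >1 to 5 mm and >5 mm.

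**Assumptions.** Ellipsoidal bleeds, the axis lengths used below, reading precision of 1 mm or 0.1 mm, and pixels of 0.4 to 0.5 mm. The SAP gives none of these, so ranges are shown.

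**1. Size of the limit.** 10 mm³ / 1,000 = 0.01 mL. The sphere of that volume has diameter (6 × 10 / π)^(1/3) = 2.7 mm. With zero bias, the SD of the differences may be at most 10 / 1.96 = 5.1 mm³.

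**2. Reading difference.** With A = B = C = d, a 1 mm change in one axis moves ABC/2 by d²/2.

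**3. Formula gap.** The exact ellipsoid volume is (π/6) × ABC. With perfect axis readings and perfect software the two methods still differ by (π/6 − 1/2) × ABC.

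| d (mm) | ABC/2 (mL) | 1 mm on one axis (mm³) | Formula gap (mm³) |
|---|---|---|---|
| 5 | 0.06 | 12.5 | 2.9 |
| 10 | 0.5 | 50 | 24 |
| 20 | 4.0 | 200 | 189 |
| 30 | 13.5 | 450 | 637 |

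The gap equals 10 mm³ at d = (10 / (π/6 − 1/2))^(1/3) = 7.5 mm, an ABC/2 volume of about 0.21 mL. At 30 mm, 10 mm³ is 0.07% of the volume and corresponds to an axis error of 20 / 30² = 0.02 mm.

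**4. Range over a sample.** Simulation of 20,000 ellipsoids per row, software volume exact, difference = software minus ABC/2:

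| Axes (mm) | Range, axes read to 1 mm (mm³) | Range, axes read to 0.1 mm (mm³) |
|---|---|---|
| 5 to 10 | −19 to +39 | +2.7 to +17 |
| 10 to 20 | −44 to +203 | +26 to +134 |
| 10 to 60 | −671 to +2,691 | −524 to +2,545 |

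None of the six ranges lies within ±10 mm³. If the formula gap is removed by using π/6 on both sides, which is not the planned method, reading to 1 mm still gives ±30, ±120 and ±730 mm³. Reading to 0.1 mm gives ±3, ±12 and ±74 mm³, so only the smallest bleeds would then pass.

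**5. Voxel size.** At 0.4 to 0.5 mm pixels, one voxel is 0.16 to 0.25 mm³ with 1 mm slices and 0.8 to 1.25 mm³ with 5 mm slices. So 10 mm³ is about 8 to 63 voxels. The obstacle is ABC/2, not the voxel grid.

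**6. The obvious alternative unit.** ±10 mL is ±10,000 mm³, 1,000 times wider, and allows an SD of 5.1 mL. A 30 × 25 × 20 mm haematoma has ABC/2 = 7,500 mm³ = 7.5 mL. Software reporting zero for it would differ by 7.5 mL, inside ±10 mL.

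**The case against.** **The section on haemorrhage extent speaks of an expected range and does not mention equivalence.** This is fair: the decision role is inferred from the general principles, which refer to limits for individual scores. The inference is sound. Those principles send the reader to later sections for the values, and the ASPECTS section uses the same language of expectation for its ±2-point limit while tying it explicitly to equivalence.

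**The superscript 3 may be a citation.** Then the limit would be ±10 mm, which is not a volume, and it would still be wrongly specified.

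**It is only a typing slip, so simply read cm³.** A slip is likely, and a reader might infer that ±10 cm³ was meant. The document does not say so, and step 6 shows that this value could exceed the whole volume of a moderate haematoma. It should not be adopted merely by changing the unit.

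**Stronger statements are tempting.** A reader might say that the limit lies below measurement resolution, or that no ABC/2 reading can agree with a voxel count to within 10 mm³. Step 5 does not support the first statement for the voxel measurement. The second is too absolute, because single pairs can agree that closely, above all in very small bleeds. What cannot realistically meet the limit is the ±1.96 SD range over the sample.

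**Little depends on it.** This stands in part. The outcome is tertiary and is to be reported separately, after the primary publication. Krippendorff's alpha and the Bland-Altman plot would still describe agreement. What is lost is the equivalence label.

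**Conclusion.** The limit is wrong as written. At ±10 mm³ (±0.01 mL), the range of differences between voxel volume and ABC/2 cannot realistically fall inside it, and error-free software would be labelled not equivalent. Formula gap alone is about 2 times the limit at 10 mm diameter (24 / 10) and 64 times at 30 mm (637 / 10); a 1 mm reading difference in one axis is 5 and 45 times the limit.

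This rests on roughly ellipsoidal bleeds with axes of 5 mm or more, read to 0.1 mm or 1 mm. The conclusion is the same across those ranges. The limit could be met only if nearly all bleeds were tiny, which is hard to expect when Table 1 lists two intracerebral haemorrhage studies, LINCHPIN (947 patients) and RESTART (537). Subdural and subarachnoid bleeds, which are not ellipsoids, would widen the range further.

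The defect itself is certain; its cause and the intended value are not. A reader might infer that the study's main conclusions are at risk. They are not, because no primary or secondary outcome, sampling step or sample size uses this number.

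**What to change.** Before the tertiary analysis, the authors should restate the intended limit in mL and give a reason for it. Two checks belong with it:

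- **Attainable:** the limit should be wider than the disagreement that ABC/2 produces on its own in bleeds of the sizes in the dataset. A calculation like step 4, run on the recorded haemorrhage dimensions without looking at software output, would show this.
- **Not too loose:** the limit should not exceed typical haematoma volumes, so that software that misses a bleed cannot pass.

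Because the disagreement grows with volume, a relative limit on the log-ratio scale would be a reasonable addition, but it is optional.

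The cost is one corrected line with its rationale in the SAP, a short check on data already held, and one extra plot if the ratio scale is used. No new scans or readings are needed for this change.

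### The overlay questionnaire does not say how the with/without order of the ten repeated scans is balanced, so order effects can be confounded with the overlay effect

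*SAP article*

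**What the plan says.** The design is in the SAP article under Tertiary outcomes, 2a (impact of e-ASPECTS on diagnostic confidence and treatment decisions).

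- **Contrast.** "We will compare responses for readers before and after ASPECTS is calculated"; a parenthesis straight after this explains that it means with and without the overlay.
- **Displays.** "The questionnaire will contain 24 cases including some repetition of the same NECT with and without e-ASPECTS overlay". Of these, "we will include 10 cases shown with and also without e-ASPECTS overlay". Two further scans appear with overlay only and two without only, and "each of these 4 cases will be displayed only once". The resulting split is stated: "Thus 12 cases will be presented with and 12 without e-ASPECTS overlay".
- **Order.** The repeats are "presented in a non-sequential order". Nothing more is said about sequence.
- **Measures against recognition.** Repeat images are altered, with left-right reversal and removal of visible extracranial parts as examples. On histories: "A unique clinical history will be provided for all 24 cases but we will limit clinical variability between repeat cases". The slices in the two showings are identical.
- **Analysis.** With versus without overlay is one of several univariable chi-squared comparisons. No term for display order, reader or scan is mentioned.

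**The concern.** When the same reader judges the same scan twice, the two answers can differ for reasons unrelated to the overlay. The reader may be more at ease with the task, may half-recognise the scan, or may be tired. Showing the repeats apart makes recognition less likely, but it does not decide which condition gets the second look. If the overlay falls second more often than first, part of any change in confidence or treatment choice belongs to the second look and is read as an overlay effect. If it falls first more often, the distortion runs the other way.

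The image changes raise the same issue. If the reversed or cropped version is mostly the overlay version, or mostly the plain one, that alteration is also tied to the contrast.

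Whether the overlay changes confidence and decisions is the whole purpose of 2a. An imbalance shared by all readers would not shrink as more readers take part; the interval would only tighten around a shifted value.

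**Working it through.** **Inputs from the article (Tertiary outcomes, 2a):** 10 scans shown in both conditions, 2 with overlay only, 2 without only.

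**Input not in the article:** d, the shift in a response proportion (for example, sure or very sure) on a second look at the same scan. I take 5 to 10 percentage points purely as an illustration.

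**Step 1: the plan's own count.** Displays: 2 × 10 + 2 + 2 = 24. Per condition: 10 + 2 = 12. Both figures reproduce. Unique scans: 10 + 2 + 2 = 14, of which 10 (71%) are repeated.

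**Step 2: second-look bias.** Let k of the 10 repeated scans show the overlay second, averaged over readers if lists differ. The overlay arm has k second looks among 12 displays, and the other arm has 10 − k. With no true overlay effect, the expected difference (with minus without) is

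bias = kd/12 − (10 − k)d/12 = (2k − 10)d/12.

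| k | Formula | d = 5 points | d = 10 points |
|---|---|---|---|
| 0 (overlay always first) | −0.83d | −4.2 | −8.3 |
| 5 (balanced) | 0 | 0 | 0 |
| 8 | +0.50d | +2.5 | +5.0 |
| 10 (overlay always second) | +0.83d | +4.2 | +8.3 |

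**Step 3: is an unplanned mix enough?** Suppose one common list is used and the order of each pair is drawn at random. An exact 5:5 split then has probability 252/1024 = 0.246. A split of 8:2 or worse, in either direction, has probability 2 × (45 + 10 + 1)/1024 = 0.109. The standard deviation of the bias over such lists is 2 × √(10 × 0.25) × d/12 = 0.26d, or 2.6 points at d = 10. Such a list is unbiased on average, but any one list can be off, and every reader of it shares the error.

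**Step 4: fatigue and learning.** These act through position among the 24 displays. In the limiting case where all plain displays come first, the mean positions are 6.5 and 18.5, a gap of 12 places. In a fully random list the gap has mean 0 and standard deviation √(50 × (1/12 + 1/12)) = 2.9 places, where 50 = 24 × 25/12 is the variance of the positions.

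**Step 5: can the analysis repair it?** A univariable chi-squared test sees only condition and response. It ignores that the same reader and scan supply both answers and it holds no information on order, so any imbalance in Steps 2 to 4 passes into the overlay contrast.

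**The case against.** The best reply is that the article is silent here rather than wrong. A reader might infer that everyone sees one fixed list with the plain version first, so that the overlay effect is in fact confounded with order. The text does not support this. It never says that all readers share one list, and the before-and-after phrase is explained at once as with and without overlay, so it names the contrast and not the sequence. An online questionnaire with mixed order could well be balanced or nearly so. Nor is every scan repeated, since four of the 14 appear once. All of that stands, and it is why the point concerns a possible bias and not an established one.

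A reader might also want a false-positive rate. None can be derived, because 2a states no reader number and no order effect. Assume 100 readers, d = 5 points and overlay always second. A paired test on 1000 pairs treated as independent, with an assumed SD of 0.6, has SE 1.9 points and rejects a null overlay about three times in four. The planned unpaired comparison of 1200 versus 1200 displays has bias 4.2 points and SE about 2.0 at an assumed 50% response, and rejects about half the time. The figure depends on the assumptions, so it carries no weight here.

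The measures against recognition deserve credit: reversal, cropping, separate histories, spacing and four single-showing scans all weaken a second-look effect. They do nothing against fatigue or learning across 24 displays.

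Finally, the outcome is tertiary, and an article may leave a display list to a fuller document. That keeps the point small. Yet this article does set out the questionnaire's presentation and analysis in detail, and says in its Conclusions that it specifies all methods in advance. In the neighbouring reader-timing study (2b) it states that each reader's cases are a random selection; for 2a it gives only the spacing rule.

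**Conclusion.** The point holds as a gap in protection. The stated order rule does not balance first condition or modified showing over scans and readers, and the planned test cannot adjust for either. Order effects can therefore be mixed with the overlay effect. The second-look part is bounded by ±0.83d over the 12 versus 12 displays and is zero under balance. This rests on one assumption, a common shift d at the second showing of each repeated scan; the 5 to 10 points used above are illustrative. The actual order, and so the size and direction of any bias, cannot be read from the document. The primary and secondary outcomes are untouched, so this is a minor improvement.

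**What to change.** In the online tool, use two mirrored lists, or randomise per reader, so that for each repeated scan half of the readers see the overlay version first. Keep the two showings apart, as already planned, and alternate which showing is reversed or cropped. Record display position.

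Analyse the ten repeated scans with a paired or mixed model that includes overlay, display order, reader and scan, in place of relying on the univariable chi-squared test. The four single-showing scans can be reported descriptively.

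The cost is a little more set-up and analysis work, with no extra readers or cases. The section on dissemination says that tertiary outcomes need further reader data and will be reported after the main paper, so on the article's own timetable the change can precede data collection. Once answers have been gathered under an unbalanced order, the two effects may no longer be separable.
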